## Abstract

**Background:**

Despite nationwide improvements in cardiovascular disease (CVD) mortality and morbidity, CVD deaths in adults with type 2 diabetes (T2DM) are 2–4 times higher than among those without T2DM. A key contributor to these poor health outcomes is medication non-adherence. Twenty-one to 42% of T2DM patients do not take blood sugar, blood pressure (BP), or statin medications as prescribed. Interventions that foster and reinforce patient-centered communication show promise in improving health outcomes. However, they have not been widely implemented, in part due to a lack of compelling evidence for their effectiveness in real-life primary care settings.

**Methods:**

This pragmatic cluster-randomized trial randomizes 17 teams in 12 Federally Qualified Healthcare Centers (FQHCs) to two experimental groups: intervention (group 1): Office-Gap + Texting vs. control (group 2): Texting only. Office-GAP (Office-Guidelines Applied to Practice) is a patient activation intervention to improve communication and patient-provider partnerships through brief patient and provider training in shared decision-making (SDM) and use of a guideline-based checklist. The texting intervention (Way2Health) is a cell phone messaging service that informs and encourages patients to adhere to goals, adhere to medication use and improve communication. After recruitment, patients in groups 1 and 2 will both attend (1) one scheduled group visit, (90–120 min) conducted by trained research assistants, and (2) follow-up visits with their providers after group visit at 0–1, 3, 6, 9, and 12 months. Data will be collected over 12-month intervention period. Our primary outcome is medication adherence measured using eCAP electronic monitoring and self-report. Secondary outcomes are (a) diabetes-specific 5-year CVD risk as measured with the UK Prospective Diabetes Study (UKPDS) Engine score, (b) provider engagement as measured by the CollaboRATE Shared-Decision Making measure, and (c) patient activation measures (PAM).

**Discussion:**

This study will provide a rigorous pragmatic evaluation of the effectiveness of combined mHealth, and patient activation interventions compared to mHealth alone, targeting patients and healthcare providers in safety net health centers, in improving medication adherence and decreasing CVD risk. Given that 20–50% of adults with chronic illness demonstrate medication non-adherence, increasing adherence is essential to improve CVD outcomes as well as healthcare cost savings.

**Trial registration:**

The ClinicalTrials.gov registration number is NCT04874116.

**Supplementary Information:**

The online version contains supplementary material available at 10.1186/s13063-022-06581-6.

## Administrative information

Note: the numbers in curly brackets in this protocol refer to SPIRIT checklist item numbers. The order of the items has been modified to group similar items (see https://urldefense.com/v3/__http://www.equator-network.org/reporting-guidelines/spirit-2013-statement-defining-standard-protocol-items-for-clinical-trials/__;!!HXCxUKc!zLkw_DQCt6R53fZ1y-ZCAHnKCwDW-5MjD0SIHX3-IepYAg7D04BjnJZ2lxT2OJF0IHjn8fq0auC6-is$).

## Introduction

### Background and rationale {6a}

The objective of this study is to decrease cardiovascular disease (CVD) risk for minority and low-income adults with type 2 diabetes (T2DM) by improving medication adherence. Despite nationwide improvements in CVD mortality and morbidity [1], CVD deaths in patients with T2DM are 2–4 times higher than among those without T2DM [2, 3]. A key contributor is medication non-adherence. Twenty-one to 42% of T2DM patients do not take blood sugar, blood pressure (BP), or statin medications as prescribed [4], contributing to increased morbidity and mortality [5]. Treatment and prevention regimens are complex, requiring innovative approaches to extending support beyond face-to-face clinic visits. Mobile health (mHealth) interventions hold promise as a scalable support strategy. However, research increasingly suggests that mHealth alone may not change behavior enough to improve health outcomes [6, 7]. In our pilot study to improve CVD care for patients with T2DM, we found that text messaging alone did not significantly improve patient activation, self-management, or medication adherence over 4 months. However, text messaging plus enhanced patient-provider communication in the Office-Guidelines Applied to Practice (Office-GAP) Program improved adherence to refills and medications compared to text messaging alone at 4 months [8].

Office-GAP is a patient activation intervention to improve communication and patient-provider partnerships through brief patient and provider training in shared decision-making (SDM) and use of a guideline-based checklist. In a pilot study under the PI’s K-award, among minority and low income T2DM and CVD patients, Office-GAP improved medication use, BP control, CVD knowledge, SDM, and patient and provider satisfaction with their communication at 6 months [9–11]. However, improvements were not sustained. A second pilot suggested that adding mobile phone texting to Office-GAP may help translate initial patient activation into long-term effective self-management [12]. We now propose to test and rigorously evaluate in a cluster randomized controlled trial, the combined Office-GAP and texting intervention (Way2Health) compared to texting alone, to determine impact on adherence to CVD treatment and prevention regimens in minority and low SES patients with T2DM [8, 13]. Our long-term goal is to reliably improve and sustain adherence in this vulnerable population to prevent CVD and eliminate disparities in CVD morbidity and mortality.

## Objectives {7}

We hypothesize that the combined intervention will improve both patient adherence and clinical outcomes over 12 months. We will randomize 17 teams in 12 FQHCs, recruiting 378 adults with T2DM to either (1) Office-GAP + Texting or (2) Texting only. Our primary outcome is medication adherence measured using eCAP electronic monitoring and self-report. Secondary outcomes are (a) diabetes-specific 5-year CVD risk as measured with the UK Prospective Diabetes Study (UKPDS) Engine score, (b) provider engagement as measured by the CollaboRATE Shared-Decision Making measure, and (c) patient activation as measured by the Patient Activation Measure (PAM).Aim 1: Compare the effects of Office-GAP + Texting intervention (group 1) with Texting only (controlling for attention) (group 2) in improving medication adherence, UKPDS risk score, provider engagement, and patients’ activation scores. Hypotheses:H1: Group 1 patients will show significant improvement compared with group 2 at 6 and 12 months in the (a) primary outcome of medication adherence, (b) secondary outcomes of UKPDS score, (c) provider engagement, and (d) patient activation scores.Aim 2: Identify barriers and facilitators to adoption, implementation, maintenance, and spread using an integrated RE-AIM and Consolidated Framework for Implementation Research (CFIR) and to explore potential mediators and moderators of effectiveness.Exploratory aim 3: Determine whether there are differences in cost and health care utilization between groups 1 and 2 using the Micro-Costing Questionnaire and The Health Services Utilization Form.

## Trial design {8}

### Design

Our trial design is a pragmatic cluster-randomized trial of the test of equality between two groups. We test for equality of effects in two parallel intervention groups (1) Office-GAP + Texting and (2) Texting only, at 6 and 12 months and for change from baseline. The null hypothesis of all two-sided tests is the equality of effects between the two intervention groups. This pragmatic cluster-randomized trial randomizes 17 practice teams to two experimental groups: intervention (group 1): Office-Gap + Texting; control: Texting only (group 2). We plan to enroll at least 22 patients per team, with the target of having 320 evaluable patients for analysis. Because intact teams are randomized to treatment condition, and not individual patients, statistical analyses of outcomes in patients require accounting for intra-cluster correlation (“between subjects”) and serial correlation (“within subjects”) in repeated measures at baseline, 6 months, and 12 months.

Two theoretical frameworks guided our intervention development, measures, and proposed analysis. The first, Self Determination Theory [14–16], suggests that effective interventions need to encourage patients to articulate their own values and goals (autonomy), agree that recommended behaviors correspond with these intrinsic values and goals (autonomous motivation) and have confidence in their ability to execute the targeted behaviors (competence), and second, Social Cognitive Theory [17, 18], which builds on the importance of understanding the quality of a health decision and of developing intrinsic motivation to change behaviors. It emphasizes patients’ self- efficacy in their ability to execute specific tasks (such as medication taking and involvement in treatment decision-making). Enhancing self-efficacy improves physiologic outcomes [12] and functioning [19]. We propose an intervention involving three interactions, forming a positive feedback loop (Fig. 1) [8].

**Fig. 1 Fig1:**
[figure not shown]
Combined interventions form a feedback loop

The first is a patient-activation intervention in which patients are introduced to the evidence guiding their treatment plan and self-management. The second is the clinical encounter as a site for shared decision-making (SDM), between patients and providers, scaffolded by a checklist. Together, these first two steps constitute the Office-GAP intervention [9–11]. The third component is a mobile health-messaging program (Way2Health) that provides patients with ongoing between visit support, information, and a means to contact their provider between visits. Unlike stand-alone mHealth interventions, the Office-GAP Program is a patient activation intervention (PAI) that educate patients and providers in SDM. The combination of Office-GAP + mHealth provides a positive feedback loop [8].

## Methods: participants, interventions, and outcomes

### Study setting {9}

We are recruiting subjects from 12 FQHCs serving minority and low-income populations in Michigan, USA [20]. FQHCs are federally qualified, community-based, and patient-directed health centers serving low-income and underserved populations. They offer access to comprehensive care regardless of a patient’s ability to pay. These clinical sites are in urban, suburban, and rural areas of the state.

#### Sample

We will recruit a total of 378 patients with the goal of having 320 evaluable participants, self-identified men, and women, with T2DM that is not well-controlled (our standard will be a score for the HbA1c test 8 or higher than 8).

### Eligibility criteria {10}

#### Inclusion criteria

Patients: aged >18 at participating FQHCs who (1) have a diagnosis of T2DM with HbA1c >8, with or without CVD; (2) are taking at least one prescribed medication for BP, diabetes, or cholesterol management; (3) are able to provide informed consent; (4) are able to read and speak English (grade 6 reading level); and (5) have a cell phone with texting (provided by our study for any enrolled patient who does not have one). Providers: All providers in the participating clinics.

#### Exclusion criteria

(1) Medical record documentation of cognitive impairment, dementia, or psychosis; (2) plans to leave the area prior to study completion; and (3) participating in another behavioral diabetes intervention.

### Who will take informed consent? {26a}

A research assistant (RA) from our study team will conduct informed consent for patients at their initial group visit. We have three RAs, one in each of the three geographical areas where our clinical sites are located.

### Additional consent provisions for collection and use of participant data and biological specimens {26b}

This trial does not involve collecting biological specimens for storage.

### Interventions

#### Explanation for the choice of comparators {6b}

The comparators in this trial are clusters in which we implement a shared-decision making protocol consisting of a group visit in which patients learn tools to increase their skills and engagement in their care (“patient activation”) followed by a checklist used by providers, and patients to guide discussions during provider visits (the Office-GAP protocol) plus text messaging or text messaging alone. These options represent our approach to implement shared-decision making with text messaging as a mechanism of reinforcement in the Office-GAP group compared to text messages without a shared decision-making intervention. In our pilot study, patients’ medication adherence improved significantly with both Office-GAP + text messaging and with text messaging after four months. In the current study, we extend the intervention to 1 year to evaluate the impact of the arms on both medication adherence and cardiovascular risk score.

We hypothesize that the combination of Office-GAP plus text messaging for reinforcement will produce significant improvement in cardiovascular risk scores over 12 months. We also hypothesize that text messaging will improve patients’ cardiovascular risk at 3 and 6 months but will produce less improvement over 12 months than Office-GAP + text messaging. This hypothesis reflects our view that text messages are most valuable as reinforcement for a care plan established by the patient and provider through shared decision-making rather than as a substitute for a care plan.

#### Intervention description {11a}

Patients in either the intervention or control group will receive medical treatment-as-usual from the participating clinics, consisting of diabetes care, usual preventive care, and other medical treatment as needed (Table 1).

**Table 1 Tab1:** Intervention components

	Physician and staff education model for all intervention groups	
	GROUP 1 PAI + Texting	GROUP 2 Texting only
**Baseline visit**	**Group visit** **• Office-GAP PAI** **• Way2Health Texting program** **• BP Check** **• Surveys and checklist use**	**Group visit** **• Way2Health Texting program Only** **• BP Check** **• Complete Surveys**
**PAI (group 1)**	**• Baseline evaluation and patients complete all study questionnaires** **• Introduction to CVD/DM and lifestyle changes** **• Discussion of benefits of using each cardiac/diabetes medication** **• Discussion of goal setting, shared decision-making, and patient engagement** **• Review of patients’ medications and completion of the** ***Office-GAP agreement*** **• Review of ACP Booklet** ***Living with Diabetes & Medication Adherence video*** **• Pre and post evaluation of the group visit**	
**Texting (Care4Life) (groups 1 and 2)**	**•** ***Medication Adherence Intervention*****:** **Way2Health sends educational messages and quizzes on medication and adherence** **User responds to quiz** **•** ***DM Self-Management*** **Way2Health sends educational messages and quizzes on DM self-management** **User responds to quiz** **•** ***Blood Sugar Control Intervention*** **Way2Health sends educational messages about healthy blood sugar** **Way2Health sends blood sugar testing reminders** **User enters blood sugar readings and receives feedback on goals** **•** ***Blood Pressure Control Intervention*** **Way2Health sends educational messages about healthy BP** **Way2Health sends reminders to check and record BP** **User enters BP readings and receives feedback on goals** **•** ***Appointment Attendance Intervention*** **Way2Health sends appointment reminders** **User confirms appointment or reschedules**	
**6 and 12 months**	**-PAI Decision checklist** **-BP Check** **-Review of texting use** **- Surveys and exit interviews**	**-BP Check** **- Review of Texting use** **-Follow-up surveys** **-Exit Interviews**

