##### At the group visit

We will obtain informed consent/HIPAA authorization from patients after introducing them to the study: Group 1: Office-GAP + Texting session: the group visit is a shared decision-making (SDM) activation session wherein patients learn self-management behaviors, communication skills, and use of decision support tools (DSTs). They also learn how to use the eCap electronic pill container to monitor medication adherence: learn to use Way2Health Texting service and confirm set up on their mobile phone. Group 2: For the texting only group: participants will learn how to use Way2Health Texting service and confirm set up on their mobile phone and learn how to use the eCap electronic pill container to monitor medication adherence. They will not experience the Office-GAP intervention. Both groups will also complete baseline study questionnaires during the group visit.

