##### Office-GAP follow-up visit with providers

The Office-GAP Checklist is the core tool of our SDM intervention. A one-page checklist, this SDM tool outlines all evidence-based medications for secondary prevention of CVD in T2DM patients. It is an in-consultation decision support tool that helps engage the patient and provider to encourage and enhance an SDM process via discussion of medication and secondary prevention/lifestyle changes during an office visit. In this study, the Office-GAP Checklist will be completed by the physician with direct patient involvement during the office visits at 0–1, 3, 6, 9, and 12 months. Only group 1 patients will use this checklist during their office visits.

The Office-GAP Checklist also serves as a physician reminder at the point of care, because the physician records a checkmark for each medication: “Yes” (if patient is on the medication), “No” (if patient is not), or “Does not apply to me because….” A reason for exclusion of a medication is also provided (patient is not eligible for the medication, has a contraindication to its use, or the patient and physician have identified an alternative due to side effect or cost concerns). Details about the next appointment and any secondary prevention plan changes are also listed on the form. At the end of the visit, both patient and physician sign the form to confirm that they have reviewed the checklist. The patient receives a copy of the checklist to take home and a copy is retained in the patient record. All providers in the intervention teams receive a brief physician education in Office-GAP tool use and communication skills.

Educational tool literacy standards: Office-GAP has been rigorously adapted for use with low health literacy patients. All study materials are grade 6 reading level.

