##### Provider and practice staff training

All intervention providers will participate in an interactive orientation which we have shown to promote behavioral change among health professionals. Providers will be asked to give their consent to participate in the study during this session. Provider/Staff Educational module: The training session is 60–90 min [22]. The session is scheduled multiple times to meet providers’ needs. In our pilot Office-GAP study, we achieved 100% participation by providers. The training module, facilitated by PI and co-investigators, includes (1) brief presentations on effectiveness and cost-effectiveness of medical therapy and behavior changes in management of T2DM, blood pressure, and heart disease; (2) a hands-on practice session for providers to elicit patients’ preferences and values; (3) an introduction to the Office-Gap Checklist and best practices for using it during a patient encounter; and (4) review of the Smith evidence-based patient-centered method for establishing trust, communicating clearly, and engaging in goal-setting with patients [22]. Providers will have a chance to practice skills using Braddock [23] and Elwyn’s [24]) approach to role-playing to model office visits; and (5) a complete pre-and post-training survey (before and after the training session) to determine provider attitudes about the use of DSTs, SDM, and mHealth in their practice and an end of study semi-structured interview.

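### The protocol is inconsistent on whether group 2 providers receive the provider education, so the contrast between the arms can be read in two ways

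*Protocol article*

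**What the plan says.** Some parts of the protocol article point to provider education in both arms:

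- Table 1 (Intervention description {11a}) carries the line "Physician and staff education model for all intervention groups".
- The Design section describes "two parallel intervention groups (1) Office-GAP + Texting and (2) Texting only" and states: "The null hypothesis of all two-sided tests is the equality of effects between the two intervention groups". Intervention groups here plainly means both arms.
- The Aim 3 cost analysis divides training costs evenly across what it again calls the intervention groups.
- Providers consent at the training session (Provider and practice staff training), and the arm is disclosed to them after consent (Concealment mechanism {16b}). Taken literally, group 2 providers would also attend.

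Other parts point to group 1 only:

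- Background and rationale {6a} says that Office-GAP works "through brief patient and provider training in shared decision-making (SDM) and use of a guideline-based checklist". The abstract says the same. Office-GAP is what differs between the arms.
- Office-GAP follow-up visit with providers: "All providers in the intervention teams receive a brief physician education in Office-GAP tool use and communication skills". The same section reserves the checklist for group 1 patients.
- Provider and practice staff training: "All intervention providers will participate in an interactive orientation". The content includes eliciting preferences, the checklist and patient-centred communication.
- Of group 2 patients, At the group visit says: "They will not experience the Office-GAP intervention". Explanation for the choice of comparators {6b} describes the comparator as texting with no shared decision-making element.

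The Design section also labels group 1 the intervention and group 2 the control, so the word *intervention* has two meanings within one section.

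**The concern.** This is the content of the comparator, and the article states it inconsistently. It is not detail left to a fuller document. Provider training is described as a component of the package under test. If control providers receive it too, the randomised difference is the patient session plus the checklist, on top of texting and trained providers. If they do not, the difference is the whole package.

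Three conclusions depend on the answer:

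- **A null result.** Under one reading it speaks to Office-GAP including provider training. Under the other it speaks only to what the session and checklist add to trained providers.
- **CollaboRATE.** This secondary outcome is the article's measure of provider engagement, and patients complete it after an encounter. The training targets the behaviour it rates, so training both arms would be expected to narrow the contrast.
- **Aim 3.** An even split of training costs suits training in both arms. If only group 1 is trained, it charges the control arm for something that arm did not receive.

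**Working it through.** **Step 1: does one consistent meaning of *intervention* remove the conflict?**

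- *Both arms throughout.* Table 1, the two training sections and the cost split then agree that everyone is trained. But group 2 providers would be taught a checklist that only group 1 uses, and would receive training that the Background counts as part of Office-GAP. That conflicts with the comparator section.
- *Group 1 throughout.* The training sections then agree with the Background and the comparator section. But Table 1 speaks of all intervention groups, in the plural, when only one group would qualify, and the cost analysis would have no second group across which to split evenly.

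Neither meaning fits every section.

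**Step 2: the two contrasts.**

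- Group 1 only trained: (texting + patient session + checklist + provider training) minus (texting).
- Both arms trained: (texting + patient session + checklist + provider training) minus (texting + provider training), which leaves the patient session + checklist.

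**Step 3: effect on Aim 3 if only group 1 is trained.** Let T be the total provider-training cost. The section Cost and healthcare utilization lists provider training as a cost-generating event.

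- Correct allocation: T to group 1 and 0 to group 2, a difference in group totals of T.
- Even split: T/2 to each, a difference of T/2 − T/2 = 0. The difference in totals is understated by T.
- Per patient, at the planned 9 × 22 = 198 and 8 × 22 = 176 patients: the correct difference is T/198 = 0.00505T. The even split gives T/396 − T/352 = 0.00253T − 0.00284T = −0.0003T.
- If evenly means equal per patient, the difference is T/374 − T/374 = 0.

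**Step 4: can a size be put on the primary outcome?** Sample size {14} gives adherence rates of 0.40 and 0.42 (group 2) and 0.40 and 0.65 (group 1) at baseline and 12 months, an ICC of 0.002, a serial correlation of 0.30, 9 and 8 teams of 22, and 83.1% power for the 12-month difference in differences.

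- Difference in differences: (0.65 − 0.40) − (0.42 − 0.40) = 0.23.
- Standard error implied by 83.1% power at two-sided 5%: 0.23/(1.960 + 0.958) = 0.079.
- Standard error from the stated inputs: design effect 1 + 21 × 0.002 = 1.042, so effective sizes are 198/1.042 = 190.0 and 176/1.042 = 168.9. With variance per arm [p(1−p) + 0.24 − 2 × 0.30 × √(p(1−p) × 0.24)]/n, the sum is 0.3273/190.0 + 0.3385/168.9 = 0.00373, and its square root is 0.061. Power is then Φ(0.23/0.061 − 1.96), about 96.5%. The stated 83.1% is not reproduced; that is a separate matter.
- Suppose, purely as an assumption, that provider training carries 25% of the effect and both arms receive it. The difference becomes 0.1725, and power is 59% with the first standard error but 81% with the second. At assumed shares of 10% and 50% the pairs are 75% against 92%, and 31% against 47%.

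The share has no source in the document, and the answer changes with the standard error chosen. No power loss can be reported.

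**The case against.** The strongest reply is that this is loose wording. The sentence just before Table 1 separates the intervention from the control group, so the heading may simply mean the Office-GAP teams. The columns that the heading spans cannot be confirmed from the text of the table. The section on the trial design also says that the patient session and the checklist-guided encounter together make up Office-GAP, and the comparator section describes the Office-GAP protocol in the same way. On that definition, training both arms would leave the named components randomised.

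Much of this stands. The point rests on the phrase in the heading, not on its position. The session and checklist do remain randomised under either reading, so a reader who infers that the trial would no longer test Office-GAP at all goes too far. But the design section itself ends by saying that the programme educates providers as well as patients, in line with the abstract and Background. The plural in the heading and the even cost split are also not explained by a group 1 reading.

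Two other inferences are tempting and unsupported:

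- A reader might say that the text restricts training to Office-GAP teams. It does not: neither training section says *only* or names group 1.
- A reader might say that the planned power holds under just one reading. Sample size {14} never mentions provider training. Its near-flat control rate (0.40 to 0.42) and its label for the control as text alone sit more easily with an untrained control, but they tie the rates to neither definition.

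**Conclusion.** The inconsistency is real and should be resolved. The article supports two descriptions of what group 2 providers receive, and so two contrasts. Group 1 only is the better-supported reading, but it is reached by inference from the definition of Office-GAP, the comparator rationale and the checklist's restriction to group 1.

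The one consequence that can be sized is in Aim 3: if only group 1 is trained, the planned split understates the difference in group totals by the entire provider-training cost. This assumes that evenly means equal halves; an equal per-patient split also leaves no training cost in the difference in mean cost. For CollaboRATE and for a null primary result, the direction of the problem is clear but its size is not. The document does not show that control providers were in fact trained, and it supports no statement about lost power.

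**What to change.** State explicitly whether group 2 providers receive the education, and bring Table 1, the two training sections and the Aim 3 cost analysis into line.

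- **If group 1 only:** change the Table 1 heading to say group 1 teams only, name group 1 in the two training sections, and assign provider-training costs to group 1. The Micro-Costing Questionnaire is already meant to record expenses by group, so no new data are needed.
- **If both arms:** word the aim and the conclusion as the patient session plus checklist added to texting and provider training, and review whether the assumed adherence rates in Sample size {14} still apply.

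In either case, report training attendance by team and arm. Using one term for both arms and another for group 1 would prevent the ambiguity from returning.

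The cost is a few wording changes and one descriptive table. Only the second case asks for more: a restated aim and a second look at the planning assumptions.
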